## Supplement 1: Knowledge and attitude scales related to HCV.

**B. Attitude questions**

**The following questions will ask about your feelings and attitudes regarding HCV. Please indicate whether you agree or disagree with the following statements.**

1. I would feel pity for someone with Hepatitis C.
   1. Strongly disagree
   2. Disagree
   3. Neither agree nor disagree
   4. Agree
   5. Strongly agree
2. I would not want my child to attend school where one of the students had Hepatitis C.
   1. Strongly disagree
   2. Disagree
   3. Neither agree nor disagree
   4. Agree
   5. Strongly agree
3. I would not want to work in an office where one of the people there had Hepatitis C.
   1. Strongly disagree
   2. Disagree
   3. Neither agree nor disagree
   4. Agree
   5. Strongly agree
4. I would not want to go to a small neighborhood grocery store where the owner had Hepatitis C.
   1. Strongly disagree
   2. Disagree
   3. Neither agree nor disagree
   4. Agree
   5. Strongly agree
5. I would feel uncomfortable wearing a sweater once worn by a person with Hepatitis C.
   1. Strongly disagree
   2. Disagree
   3. Neither agree nor disagree
   4. Agree
   5. Strongly agree
6. I would feel uncomfortable sharing a meal with someone who has Hepatitis C.
   1. Strongly disagree
   2. Disagree
   3. Neither agree nor disagree
   4. Agree
   5. Strongly agree
7. I would not want to be friends with someone with Hepatitis C.
   1. Strongly disagree
   2. Disagree
   3. Neither agree nor disagree
   4. Agree
   5. Strongly agree
8. I would not employ someone with Hepatitis C to work for me.
   1. Strongly disagree
   2. Disagree
   3. Neither agree nor disagree
   4. Agree
   5. Strongly agree
9. I would feel uncomfortable having a conversation with someone who had Hepatitis C.
   1. Strongly disagree
   2. Disagree
   3. Neither agree nor disagree
   4. Agree
   5. Strongly agree
10. I would not kiss someone with Hepatitis C.
    1. Strongly disagree
    2. Disagree
    3. Neither agree nor disagree
    4. Agree
    5. Strongly agree
11. I would not date someone with Hepatitis C.
    1. Strongly disagree
    2. Disagree
    3. Neither agree nor disagree
    4. Agree
    5. Strongly agree
12. I would not marry someone with Hepatitis C.
    1. Strongly disagree
    2. Disagree
    3. Neither agree nor disagree
    4. Agree
    5. Strongly agree
13. I would avoid rooming with someone with Hepatitis C.
    1. Strongly disagree
    2. Disagree
    3. Neither agree nor disagree
    4. Agree
    5. Strongly agree

**D. Knowledge**

1. People with hepatitis C can safely share their toothbrushes and razors with others.
   1. True
   2. False
   3. I don't know
2. The consumption of alcohol by people with hepatitis C can damage the liver.
   1. True
   2. False
   3. I don't know
3. People who underwent transfusion of blood products, may have been infected with hepatitis C.
   1. True
   2. False
   3. I don't know
4. The hepatitis C vaccine can be used to prevent new infections with this virus.
   1. True
   2. False
   3. I don't know
5. People who inject drugs with "used needles" are infected with hepatitis C.
   1. True
   2. False
   3. I don't know
6. People infected with hepatitis C may not be aware of the infection for many years.
   1. True
   2. False
   3. I don't know
7. People who use nasal cocaine are at risk of transmitting hepatitis C through the use of shared straws, rolled up banknotes, etc.
   1. True
   2. False
   3. I don't know
8. Using new, never used needles, syringes and other equipment reduces the risk of hepatitis C infection.
   1. True
   2. False
   3. I don't know
9. The baby may be infected by a mother who was infected with hepatitis C during delivery.
   1. True
   2. False
   3. I don't know
10. May be infected with hepatitis C through sexual contact.
    1. True
    2. False
    3. I don't know
11. Effective HCV antiviral therapy can completely eliminate the virus from the patient's blood.
    1. True
    2. False
    3. I don't know
12. Hepatitis C can be spread by sharing kitchenware (cups, plates, cutlery, etc.).
    1. True
    2. False
    3. I don't know
13. People after successful HCV antiviral therapy and viral eradication cannot be re-infected with this virus.
    1. True
    2. False
    3. I don't know
14. Hepatitis C infection may occur during tattooing or piercing.
    1. True
    2. False
    3. I don't know

## Supplement 2: Study protocol

**Expanding HCV test uptake using HCV self-testing among men who have sex with men in China: study protocol for two parallel randomized controlled trials**

**Abstract**

**Background:** Men who have sex with men (MSM) bear a disproportionate burden of infection with Hepatitis C virus (HCV), especially for MSM living with HIV. Low rate of HCV testing is a major public health issue among MSM in many low- and middle-income countries. We designed this study to evaluate the effectiveness and cost-effectiveness of providing HCV self-testing (HCVST) to increase HCV testing uptake among HIV-negative MSM and MSM living with HIV in China.

**Methods:** Two parallel, unmasked, individual-level, randomized controlled trials will enroll MSM who had a HIV-negative result report in the past three months (trial 1) and MSM who had a HIV-positive result report (trial 2) from seven community-based organizations in seven provinces in China. In each trial, participants will be randomly assigned in 1:1 ratio into one of two arms: standard of care (SOC) arm and HCVST arm. The SOC arm will receive a community-based message and postcard to encourage them to test for HCV at local clinics. In addition to the message and postcard for men, we will provide men in the HCVST arm with free HCVST kits. All MSM will complete a baseline survey and a four-week follow-up survey. HCV test results will be determined by photo verification through a digital platform.

**Conclusion:** Findings from this study will be used to explore whether HCVST can increase testing rates compared with traditional facility testing services and improve the early diagnosis rate of HCV among MSM.

**Trial registration:** Chinese Clinical Trial Registry, ChiCTR2100048379.

**Key words:** HCV, Self-testing, Randomized controlled trial, Men who have sex with men

**Background**

HCV is a public health concern with a global goal to be eliminated by 2030 set by World Health Organization (WHO)[1]. In 2019, there were 58 million people with chronic HCV infection globally, but only 21% were diagnosed[1]. Untreated HCV infection can lead to death due to liver cancer, fulminant hepatitis, liver cirrhosis and other complications[1]. MSM are disproportionately affected by HCV infection[2], especially HIV-positive MSM with high-risk behaviors such as condomless anal sex or injection drug use [3]. A global systematic review found the prevalence of HCV in MSM living with HIV was 6.3% (95% CI: 5.3 to 7.5) compared to 1.5% (95% CI: 1.0 to 2.1) in HIV-negative MSM[4]. In China, a meta-analysis estimated that HCV prevalence was 1.2% and 8.4% among general MSM and MSM living with HIV, respectively[5].

Expanding HCV testing is critical for HCV control[3]. WHO recommends all MSM should receive HCV testing at least once every year[6]. Studies suggest that only 41% of Chinese MSM have been tested for HCV in their lifetime[7], which was 49% lower than WHO’s target[8]. Previous studies showed that perception of HCV as low risk and fear of stigma and discrimination from health care providers contributed to the low uptake of HCV testing among MSM[9]. Additionally, inconvenience and lack of privacy for facility-based HCV testing, unlinked systems for HIV and other STDs, and COVID-19 restrictions also led to low HCV testing uptake [10, 11]. In response to these gaps, the latest guideline from WHO strongly recommends HCVST as a potential method to enhance uptake of HCV testing among MSM[12].

HCV self-testing (HCVST) is a process in which an individual collects their specimen (blood or oral fluid), performs a simple rapid diagnostic test, and then interprets their result in a private setting, either alone or with someone they trust[12]. Several studies in Egypt[13] and Vietnam[14] have demonstrated high usability, acceptability and feasibility of using HCVST among MSM, which provides a strong foundation to support the promotion of HCVST.

HCVST kits have been approved for HCV screening in China, which can be accessed through e-commerce platforms (Taobao and Jingdong). However, there are limited studies to evaluate the effectiveness and cost-effectiveness of HCVST compared to traditional facility-based testing. The purpose of this protocol is to design two parallel randomized controlled trials to evaluate the effectiveness and cost of providing HCVST on increasing the frequency of HCV testing compared with standard-of-care: one in HIV-negative MSM (trial 1) and one in MSM living with HIV (trial 2) in China.

**Methods**

**Study design**

Two parallel, unmasked, individual-level, randomized controlled trials will be conducted among MSM. All enrolled MSM will be offered to join one of the two trials according to their HIV status. In trial 1, we will enroll MSM who had a HIV-negative result according to their testing report in the past three months. In trial 2, we will enroll MSM who had a HIV-positive result determined by testing report. In each trial, all participants will be randomly assigned in a 1:1 ratio into one of two arms: standard of care (control arm) and HCVST. The SOC arm will receive a community-based message and postcard to be encouraged to take anti-HCV IgG testing at local clinics. In addition to the message and postcard for men in the SOC arm, the HCVST arm will be provided with free HCVST kits during the study period. Participants in each arm will be followed for four weeks (Fig. 1). Preliminary data from a pilot study will be used to inform the final trial design.

**Study setting and population**

Participants are eligible if they are born biologically male, age 18 years or above, having anal sex with other men, reporting not testing for HCV in the past year, reporting at least one of the following risk factors in the past year (condomless anal sex or STD diagnosed or injection drug use), plan to live in China for the next month and have a stable residence where they can securely receive a postal package. Participants are excluded if they are participating in similar clinical trials or other programs involving HCV testing or unwilling or unable to comply with all the requirements of the study. All enrolled participants will be divided into the two trials according to their HIV status. All participants will be recruited from seven MSM-led clinics run by MSM-focused community-based organizations(CBOs) in seven provinces located in different parts of China: East China (Shandong Province), [South China](https://en.wikipedia.org/wiki/South_Central_China) (Guangdong Province), [Northeast China](https://en.wikipedia.org/wiki/Northeast_China) (Liaoning Province), Northwest China (Qinghai Province), Central China (Hubei Province), Southwest China (Chongqing), and North China (Hebei Province). All the MSM-led clinics offer free HIV and syphilis testing and counseling for MSM. Staff at each CBO site also have rich experience in HIV/syphilis counseling and intervention. All the MSM living with HIV will be recruited offline and HIV-negative MSM will be recruited by half of the online and offline ratios through CBOs. All study sites will follow the same research procedure.

All participants will be asked to finish a baseline survey for eligibility screening through Wenjuanxing (an online survey platform belonging to Changsha Ranxing Information Technology Co., Ltd, China). Online informed consent will be obtained before the baseline survey by clicking on a “button” indicating that the participant has read the consent form and agrees to participate in this research.

**Randomization and allocation**

All eligible individuals who complete the baseline survey and provide contact information will be assigned to one of the two arms in a 1:1 ratio using a randomized block design. A separate randomization procedure will be used for each NGO to generate 12 HCVST/SOC randomized assignments for trial 1 (HIV-negative MSM) and 12 HCVST/SOC randomized assignments for trial 2 (MSM living with HIV). The final randomization schedule will be generated by a statistician who is not involved in participant recruitment, using SAS version 9.4 (SAS Institute, Cary, NC, USA). Statisticians who analyze the data will be the only blinded people in this study.

**Arms and interventions**

Arms and interventions are summarized in Table S1.

**Table S1. Arms and interventions information**

| **Arm** | **Intervention** | **Intervention delivery** |
| --- | --- | --- |
| **Standard of care** | **Health promotion**:  1) community-engaged information about the risk of HCV infection（including a message and a postcard）.  2) recommendation to undergo anti-HCV IgG testing at local clinics. | - Message and postcard will be sent at enrollment via WeChat. - Voluntary report of testing results to the platform. |
| **HCVST** | **Health promotion**:  1) community-engaged information about the risk of HCV infection（including a message and a postcard）.  2) recommendation to undergo anti-HCV IgG testing at local clinics.  **Self-testing**: free home delivery of a self-testing package if participants apply for it. | - Message and postcard will be sent at enrollment via WeChat. - Provision of HCV self-testing service for free: self-testing package can be ordered online and sent to the participant through postal mail. Maximum one self-testing package per participant. - Voluntary report of testing results to the platform. |

***SOC arm***

Participants will receive a message and a postcard about basic HCV transmission and prevention knowledge through WeChat. The message uses concise language to encourage MSM to be tested for HCV. To better engage the MSM community and make the message more accessible to them, we invited three MSM-focused CBOs leaders and ten community members to create the message, and finalized the message based on their feedback. The postcard was developed through a national crowdsourcing contest in China in 2017 with vivid expressions to introduce knowledge about HCV transmission and infection risks. It was later proven to effectively promote HCV testing among MSM[15]. We will also provide recommendations for anti-HCV IgG testing at local clinics on the postcard.

***HCVST arm***

In this arm, participants will receive SOC arm interventions. Additionally, participants in this arm will be offered HCV self-testing kits for free. Participants can order self-testing packages online and apply for free home delivery through WeChat or Wenjuanxing and are allowed a maximum of one self-testing package for the duration of the study. Each HCV self-testing package contains equipment for blood sample collection, quick HCV test and a step-by-step pictorial instruction and operation video for using the self-testing kit. The provision of HCV self-testing service will last for four weeks. In this study, we will use the ABON HCV Hepatitis C Virus Antibody Rapid test kit, which advertises a sensitivity and specificity of 99.53% and 99.78%, respectively[16].

**Follow-up support**

An HCV counselor will be in charge of care support through WeChat or telephone (office hours: 8:00 am to 5:30 pm, Monday to Friday). Care support will include HCV pre-test counseling, instruction for the HCV self-testing kit, explanation of testing results, advice on reactive testing results and other relevant emergencies. All the inquiry logs will be kept. Participants are advised to inform the HCV counselor of any reactive self-testing results and will be referred to the designated hospital for confirmatory laboratory testing and clinical examination based on the standard protocols of the respective clinics. If participants are diagnosed with HCV, further follow-up will include HCV confirmatory testing and treatment information.

**Outcome**

***Primary outcome***

The primary outcome is the HCV testing rate (including facility testing and self-testing) within four weeks, excluding confirmatory tests after a positive self-test. All testing results will use photo verification for validation. A participant will only be counted as having the primary outcome if the participant has submitted a photo including age, test date, and anti-HCV IgG results to research team through WeChat or the online platform.

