**Data collection**

***HCV testing record and results***

HCV testing results can be either from self-testing or facility-based testing. HCV self-testing will be confirmed by photo verification of the used testing kit. Facility-based HCV testing and the result will be confirmed by photo verification of the test report. Participants can securely upload testing results through WeChat or Wenjuanxing Platform. A research assistant will conduct the verification process by checking the uploaded photos. Participants in all arms who upload photo verification will get 5 RMB (approximately equal to 0.8 USD dollars). All participants will be informed at enrolment that cost of HCV testing including facility-based HCV antibody testing and HCV self-testing during the four-weeks study period can be reimbursed by providing a photo of test report and receipt.

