Several other challenges may be encountered during the study implementation. First, participants in HCVST arm will be provided HCV self-testing kits for free, while participants in SOC arm need to pay for their HCV test, which could lead to a different level of testing incentive and reduce the comparability between the two arms. Therefore, all the participants will be informed that cost of any facility-based HCV testing during the four-week period can be reimbursed by providing their test report and receipt to the investigator. Second, HCVST may not adequately connect users with post-testing services, such as confirmatory testing and management of those who test users. In this study, all participants will be recruited through a local CBO, which could be helpful for the subsequent linkage to care. Third, the four weeks duration of follow-up will limit the ability of the study to assess the long-term effect of the intervention on HCV. Fourth, to protect the confidentiality of MSM, especially for MSM living with HIV, names and other specific identifying information will not be collected. All data will be encrypted and stored in remote repositories.

Another potential limitation of this study is the potential for sampling bias since the participants will be recruited through CBOs. Thus, this recruitment strategy will exclude participants who are less likely to visit these CBOs[21]. Besides, all the recruitment sites are in the central district of cities, which may also lead to sampling bias and restrict the generalizability of results to MSM living in non-urban settings.

In conclusion, this study will compare the effectiveness and cost-effectiveness of HCVST and traditional facility testing services among HIV-negative and MSM living with HIV. Finding from this study will help explore whether HCVST can make up for the shortcomings of traditional facility testing services by improving the early diagnosis rate of HCV.

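### The primary outcome requires a photo showing age, test date and result, but a self-test is proved by a photo of the used kit, and no step puts age or date into that photo

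*Protocol*

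**What the plan says.** Protocol, Primary outcome, defines one endpoint covering both test types: "The primary outcome is the HCV testing rate (including facility testing and self-testing) within four weeks, excluding confirmatory tests after a positive self-test". It sets one counting rule for both: the participant counts only if he "has submitted a photo including age, test date, and anti-HCV IgG results to research team".

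Protocol, HCV testing record and results, sets the proof separately by test type. For self-tests: "HCV self-testing will be confirmed by photo verification of the used testing kit". For facility tests: "Facility-based HCV testing and the result will be confirmed by photo verification of the test report". On who decides: "A research assistant will conduct the verification process by checking the uploaded photos". No acceptance criteria are given for either type.

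Protocol, Randomization and allocation, on masking: "Statisticians who analyze the data will be the only blinded people in this study". The photo checker is therefore not blinded.

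Protocol, HCVST arm, lists the package contents as blood-collection equipment, the rapid test, pictorial instructions and a video. It mentions no label, code, or instruction to write down age or date. The Discussion describes the proof that earns the cash reward more loosely, as results or other certification of testing.

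**The concern.** A facility report can carry age, date and result together. A used rapid-test device shows a result line. Nothing in the plan adds the user's age or the test date to the picture, yet the counting rule makes all three a necessary condition. Faced with a photo of a kit alone, a checker who follows the Primary outcome section rejects it, and one who follows the data-collection section accepts it. Both are following the protocol.

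The primary endpoint of both trials depends on that decision. Free kits go only to the HCVST arm, so test type is closely tied to arm, and a rule that works differently by test type works differently by arm for the most part. The same count is the denominator for the cost per person tested.

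**Working it through.** **Step 1. The two rules side by side.**

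| | Facility test | Self-test |
|---|---|---|
| What is photographed | test report | used kit |
| Result visible | can be | yes |
| Test date visible | can be | only if added |
| Age visible | can be | only if added |
| Step in the plan that adds them | not needed if printed | none stated |

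The entries for the kit are an inference from what a used device is. The Protocol does not say that the photo lacks age and date.

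**Step 2. Direction of error.**
- Rule applied strictly: valid self-tests are dropped, mainly in the HCVST arm, and the difference is understated.
- Rule relaxed for kits only: self-tests pass on less proof than facility tests. The photo then does not place the test within the four weeks, and the difference may be overstated.

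Nothing in the documents says which would happen.

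**Step 3. Reproduce the plan's own figures (Protocol, Sample size).** Inputs: two-sided Fisher's exact test, alpha 0.05, 42 per arm, 10% in SOC, and a 32-point difference, which gives 42% in HCVST.
- Exact enumeration gives power 0.910, and the Walters arcsine approximation gives 0.897. Both agree with the stated 90%.
- The pilot-based sizes also reproduce. Walters gives 13 per arm (15/19 versus 2/19) and 21 per arm (40% versus 0%). With 20% loss, 13/0.8 = 16.25, rounded up to 17, and 21/0.8 = 26.25, rounded up to 27, as stated.

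The sample size is not in question here.

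**Step 4. Illustrate the strict reading.** Let v be the share of HCVST-arm tests whose photo meets the rule. The documents give no value for v, so the values below are assumed. It is also assumed that all HCVST-arm tests are self-tests, that every SOC test meets the rule, and that all 42 per arm are analysed.

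Counted HCVST rate = v × true rate.

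| Scenario | v | Counted HCVST rate | SOC rate | Power |
|---|---|---|---|---|
| 42% vs 10% | 1.00 | 42.0% | 10% | 0.91 |
| | 0.90 | 0.90 × 42 = 37.8% | 10% | 0.83 |
| | 0.75 | 0.75 × 42 = 31.5% | 10% | 0.62 |
| | 0.50 | 0.50 × 42 = 21.0% | 10% | 0.21 |
| Trial 1 pilot rates | 0.75 | 0.75 × 78.9 = 59.2% | 10.5% | 0.998 |
| | 0.50 | 0.50 × 78.9 = 39.5% | 10.5% | 0.85 |

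In the 42% versus 10% case the counted difference falls from 32 points to 27.8 at v = 0.90 and to 21.5 at v = 0.75. The estimate is biased as well as less well powered.

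The relaxed reading cannot be illustrated in the same way, because the documents give no basis for how many unqualified kit photos would be accepted.

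**The case against.** The strongest reply is that the two sections are compatible. One says what the photo must include and the other says what is photographed, so a kit beside a handwritten age and date satisfies both. This stands against calling the rules mutually exclusive. It does not close the gap, because no section tells the participant to do this or tells the checker what to do when he has not.

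A reader might also infer three stronger things that the documents do not support.

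- **That no self-test would count, so HCVST testing would fall to the facility level of about 10%.** This needs every kit photo to fail, and facility testing in the HCVST arm to equal the SOC pilot rate. Nothing suggests the first, and the second is not given. A matching claim that SOC would lose half its roughly four testers (42 × 0.10 = 4.2) is equally unsupported, since a facility report can carry all three items.
- **That the flaw favours HCVST.** This is true only if the rule is relaxed for kits alone. The problem also follows test type rather than arm: HCVST participants are also advised to test at clinics, and all participants are told that self-test costs can be reimbursed.
- **That a kit photo cannot be tied to a participant or to the four weeks.** The Discussion does say that "names and other specific identifying information will not be collected". But contact information is provided before randomisation, kits are ordered and photos returned through WeChat or Wenjuanxing, and each man may have at most one package. A kit mailed by the study cannot be used before dispatch, and the upload sets the latest date. These links exist, but the counting rule does not use them. They do not show who used the kit.

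The Discussion also acknowledges that unreported tests will lead to underestimation, and offers reminders and a reward. That addresses tests with no photo, not photos that fail the rule. At the Trial 1 pilot rates, power stays high even with sizeable losses. The plan itself, however, warns that the pilot effects may be exaggerated.

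**Conclusion.** The point holds as a mismatch in the definition of the primary event. As written, two checkers could each follow the Protocol and count different numbers of tested participants. This goes beyond operational detail, because a stated necessary condition meets a stated form of proof that does not by itself satisfy it, and an unblinded person has to resolve the difference.

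The direction and size of any bias cannot be fixed from the documents. The illustration gives power of 0.83 at 90% qualifying photos and 0.62 at 75%, against 0.91 with none lost. It rests on assumed shares, on the 42% versus 10% scenario, on all HCVST-arm tests being self-tests, and on complete follow-up. It shows that modest photo failure could matter, not that it will occur.

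**What to change.** Reconcile the Primary outcome section with the HCV testing record section by setting one standard for both test types and both arms: the result, a test date within the four-week window, and a link to the participant's study record.

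- **Facility test:** a photo of the dated report, uploaded from the participant's account.
- **Self-test:** a photo of the used kit beside the package code with the date handwritten, supported by dispatch and upload times. A kit the participant bought himself has no package code, so a study code issued at enrolment can take its place.
- **Age:** drop it as a condition for both test types, so that neither is held to an item the other need not show.
- **Checking:** put these criteria in writing for the research assistant. The photo reveals the test type, so a fixed rule protects the comparison better than masking could.
- **Sensitivity analysis:** repeat the primary comparison counting photo-verified tests plus tests self-reported within four weeks. The follow-up survey already asks time, method and result, so no new data are needed.

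The cost is a label and one instruction line per package, at most one package per man, plus revised outcome wording. The downside is a few re-upload requests where the code or date is missing.
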